## Abstract

**Background:**

In intensive care units (ICUs), nosocomial infections are prevalent conditions and they have been related to high mortality indexes. Some studies have suggested that inefficient oral hygiene and ventilator-associated pneumonia (VAP) are related. Nowadays, in the Brazilian public health system there is no well-defined protocol for oral hygiene in an ICU. Due to the drawbacks of the use of antibiotics, photodynamic therapy (PDT) has emerged as an interesting technique in order to reduce antimicrobial-resistant pathogens. Methylene blue (MB) is the most common chemical agent for PDT in Brazil. However, new formulations for improved effectiveness are still lacking. The objective of this study is to evaluate the use of an MB mouthwash as an effective oral-hygiene procedure in an ICU and to show that oral hygiene using PDT with MB mouthwash may reduce VAP frequency to rates similar to, or higher than, chlorhexidine.

**Methods:**

Phase 1 will evaluate the most effective cleaning procedure, while phase 2 will correlate oral hygiene to VAP incidence. At the start of phase 1, the ICU patients will be randomly allocated into three different groups (10 patients/group): the efficacy of chlorhexidine, classical MB-PDT, and mouthwash MB-PDT will all be measured for the quantification of viable bacteria, both pre- and post-treatment, by a Reverse Transcription Polymerase Chain Reaction (RT-PCR). In phase 2, the most effective procedure found in phase 1 and a mechanical cleaning with filtered water will be carried out daily, once a day, over 5 days, with a total of 52 ICU patients randomly allocated into the two groups. The clinical records will be evaluated in order to find any pneumonic diagnoses.

**Discussion:**

Since a variety of bacterial species are related to VAP, a universal primer for bacteria will be used in order to quantify the total bacteria count in the participants’ samples. In order to quantify only the living bacteria before DNA extraction, the samples will be treated with propidium monoazide. This will infiltrate the dead bacteria and will intercalate the DNA bases, avoiding their DNA amplification. This will be the first trial to evaluate MB-PDT in a mouthwash formula that can increase the effectiveness due to the control of MB aggregation. The results of this study will be able to generate an easy and low-cost protocol to be used in an ICU for the Brazilian public health system.

**Trial registration:**

This protocol was approved by the Research Ethics Committee of the Conjunto Hospitalar do Mandaqui (1.317.834, CAAE: 49273515.9.3001.5551) and it was registered in Registro Brasileiro de Ensaios Clínicos (ReBEC number: RBR-94bvrc;). First received: 12 July 2015; 1st version 6 June 2016. Data will be published in a peer-reviewed journal.

**Electronic supplementary material:**

The online version of this article (doi:10.1186/s13063-017-2133-y) contains supplementary material, which is available to authorized users.

## Background

It has been proposed that the oral cavity may be the dissemination focus of potentially pathogenic organisms to other body locations [1–4]. In intensive care units (ICU), infectious diseases are prevalent and they are responsible for the high mortality index of inpatients. The lung is the most affected organ mainly due to mechanical ventilation [5]. Ventilator-associated pneumonia (VAP) is defined as pneumonia in a patient receiving mechanical ventilation for at least 48 h that is not pre-existent at the moment of intubation [6]. The most prevalent pathogenic agents related to pneumonia are *Pseudomonas aeruginosa* 30.1%), *Staphylococcus aureus* (19.6%), *Acinetobacter* spp. (13.0%), *Klebsiella* spp. (9.5%) and *Enterobacter* spp. (8.4%) [7]. Both VAP control and prevention are important in an ICU since this can reduce hospitalisation time and costs [8].

During a patient’s stay in an ICU, oral biofilms and tongue coating increase simultaneously. Due to the orotracheal intubation, a patient’s mouth is open during the entire period, increasing bacterial plaque formation and reducing saliva flow. Consequently, this reduces the innate defence system and increases the risk of VAP [5]. Therefore, oral hygiene in an ICU is essential when implementing VAP-prevention strategies. However, developing these new strategies is a challenge, since many substances that have been suggested are associated with bacterial resistance; for example, chlorhexidine [9, 10].

In this context, photodynamic therapy (PDT) has shown effective results in killing microorganisms by a suitable combination of a photosensitiser dye, light and oxygen [11–19]. PDT’s advantages over other antimicrobial treatments are an efficacy that is independent of microorganism resistance and its broad spectrum of action. This is because a photosensitiser can act on bacteria, fungi, viruses, parasites, etc. [11, 16, 20–24]. This technique is minimally invasive, with no collateral effects to the host and it can be considered to be economically viable. The topical application of a photosensitiser is interesting since it is in direct contact with the microorganisms and it causes low collateral effects in the patient [12, 25]. In PDT treatment, after light absorption by the photosensitiser and the generation of excited states, two main photochemical mechanisms of damage to biomolecules are involved: in Type-I reactions, due to electronic transfer, the photosensitiser in its triplet excited state generates reactive oxygen species (mainly radicals); in Type-II reactions, there is the generation of singlet oxygen after energy transfer (^1^O_2_) [19]. The reaction type can affect the therapeutic efficacy since the reactivity to the targets can differ considerably [19, 26]. However, there is a lack of information regarding the relationships between the photochemical mechanisms and the inactivation efficiencies in different microorganisms. While some articles have affirmed that singlet oxygen is the main oxidising agent [27], others have suggested that reactive oxygen species (mainly radicals) are more effective at killing Gram-negative bacteria and that singlet oxygen is more effective at killing Gram-positive bacteria [21, 28].

Since microorganism membranes are negatively charged, the photosensitiser must be positively charged in order to efficiently penetrate these membranes [29]. Therefore, methylene blue (MB) has been broadly used due to its positive charges, its effectiveness and its low cost [30, 31]. Besides, MB has been frequently used in medicine, since its safety and toxicity are well known and the concentrations used in PDT are lower than those used for other medical purposes [32–35]. Methylene blue has been shown to be effective against bacteria, viruses, parasites and fungi [22, 36–39]. However, the efficacy is dependent on the microorganisms (structure, thickness and the composition of the biofilm matrix, efflux pumps, etc.) and on the treatment parameters such as MB concentrations and irradiance [29, 40–42]. Besides, the MB vehicle can affect the efficacy of PDT, although this is rarely considered. Depending upon the physicochemical environment, MB may aggregate and this feature modulates the photochemical reactions [43, 44]. While MB monomers generate singlet oxygen, MB dimers induce the production of other reactive oxygen species, mainly radicals [43]. Some studies have shown ways to control MB aggregation and these strategies can be used in order to develop specific MB formulations in which monomers or dimers are preferred [43, 45–49]. For example, Nunez et al. showed a greater ionic strength in physiological media and that saliva induced the formation of MB dimers, reducing their efficacy [46]. On the other hand, urea drives monomer formation and enhances MB PDT effectiveness [45]. Based on this information, we have designed a mouthwash formula containing MB with the aim of stabilizing MB monomers and improving the PDT outcomes. The mouthwash formula is under a patent requirement.

Regarding these circumstances, the objective of this study will be to compare classical PDT with MB in water to a mouthwash formula for oral-hygiene procedures for ICU patients. The outcome to be measured will be the oral bacteria count, measured in pre- and post-intervention samples, with three experimental groups, by using a Reverse Transcription Polymerase Chain Reaction (RT-PCR) in samples pre-treated with propidium monoazide (PMA). Finally, it is also an objective of this work to show that oral hygiene using PDT with MB mouthwash may reduce VAP frequency to rates similar to, or higher than, chlorhexidine. The outcome will be to constitute a VAP diagnosis by checking the patients’ medical cards, after 5 days of daily oral-hygiene procedures. The results of this protocol will yield interesting tools that will raise attention to ICU oral-hygiene procedures. Additionally, it will establish an easy and low-cost oral-hygiene protocol to be used in an ICU for the Brazilian public health system, as well as being an important observation regarding the MB vehicle in PDT clinical protocols.

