## Methods

### Study design

This study will be a randomised controlled, double-blind, single-centre, clinical trial. This study protocol was written based upon the Standard Protocol Items: Recommendations for Interventional Trials (SPIRIT) guidelines (see Additional file 1) and will be carried out at an ICU of a hospital in the Brazilian public health system in the city of São Paulo, Brazil (Hospital Assembly of Mandaqui). Since the patients will be unconscious during the procedures, the oral-hygiene procedures will be conducted by researcher [name], together with a sample collection by researcher [name], both authors of this protocol study. This trial can be considered to be double blind. For better understanding, this study will be described in two phases, although two different studies will be performed, nested into each other. In phase 1, PDT with an MB mouthwash will be compared to PDT with MB in water, using chlorhexidine as positive control for oral hygiene. In phase 2, the frequencies of VAP occurrence will be measured in the two groups: (1) the most effective procedures found in phase 1 group and (2) the mechanical cleaning with filtered water group.

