### Sample size calculation

First, a published paper using the same method of sample analyses (PCR + PMA pre-treatment) is to be used to determine the effect size (*Δ*). The largest and the smallest mean values (1.69 and 0.27, respectively), as well as the standard deviation (*σ* = 0.36) of the PCR quantification of living bacteria using PMA were taken from the Àlvarez article, 2013 [50]. The *n* value is to be the number of treatment groups, i.e., 3:$$ \varDelta =\frac{Largest- smallest}{{\left(\frac{\sigma }{\sqrt{n}}\right)}^2}=\frac{1.69-0.27}{{\left(\frac{0.36}{\sqrt{3}}\right)}^2}=32.8 $$

G*Power software (version 3.1.9.2, Dusseldorf, Germany) was used to calculate the sample size. Using the calculated effect size, *F* tests will be chosen for the repeated measures and for the within-between interactions. Three groups will be studied and each group will be measured before and after the oral-hygiene procedures (i.e. three groups and two measurements). The sample size was determined by setting a two-sided error at 5% and the test power at 95% of the test. According to the calculations, a sample of six patients per group will be necessary in order to detect the differences in oral hygiene in phase 1. When considering this result and the possibility of difficulties in the sample processing, phase 1 will be conducted with 10 patients per group.

The sample size calculation for phase 2 was based on the percentages of patients with VAP before and after the implementation of oral-dental care, as published by Garcia et al. [8]. Using G*Power software, when choosing the Exact Family Test and Fisher’s Exact Test as statistical tests (inequality, two independent groups) and by inserting the proportions of 0.086 and 0.041 [8], the sample size was found to be 52, i.e. 26 patients per group. It is important to highlight that at this phase, a 5-day protocol will be evaluated. Due to the condition of the patients, some of them may recover and the mechanical ventilation will be removed, while some may get worst or even die. Due to these potential dropout patients, a sample size of 70 patients (35 per group) will be used.

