Within 24 h of the start of the mechanical ventilation and after checking the patients’ eligibility and obtaining the Consent Form signed by the person responsible for the patient, the intervention will be conducted. First, a patient’s sample will be collected by [name]. Following this, the oral-hygiene procedure will be performed by [name] with a gauze (7.5 cm × 7.5 cm size and sterile) soaked in a solution that will be determined by randomisation: (1) positive control group: chlorhexidine 0.12%, (2) MB 0.05% aqueous solution, (3) MB 0.05% blue mouthwash (this will be prepared in a pharmacy – the formula is under patent requirement). Oral hygiene will be initiated from the right upper arcade (the labial surface), passing to the left arcade (no return). Then, the palatal hygiene will be conducted from left to right. When the upper arch has been completed, the left buccal mucosa will be hygienised, then the lower arch moving from left to right. At conclusion, the mouth floor, the tongue and the lips will be hygienised (due to the dryness caused by the salivary reduction). After the mechanical cleaning and the active application of mouthwash, 5 min of incubation will be necessary before starting the light exposures. The light system will be a Lineaxul Bucal (Cosmedical, Brazil) which is a light-emitting diode (LED) device emitting at the red region of the spectra (660 nm). The device is a flexible lollipop-shaped instrument composed of six LED points on both sides, allowing for simultaneous illumination. Three devices will be used simultaneously: one above the tongue, promoting the illumination of the palate region and two others positioned on the buccal mucosa (right and left). Using this composition, the oral cavity will be illuminated as a whole for 15 min. Another sample will be collected by sterile swabs soaked in a physiological solution (sodium chloride 0.9%), 30 min after the procedure in the retromolar trigone region. These swabs will be stored in sterile tubes containing Tris-EDTA buffer (Tris 10 mM, pH 8, EDTA 1 mM) and will be identified with a patient number (received at randomisation) and a pre- and post-treatment label (T_0_ – before treatment; T_1_ – after treatment) [35]. Any modifications in the protocol will be informed in the results paper.

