**Fig. 1 Fig1:**
[figure not shown]
Phase-1 flow diagram

#### Interventions in phase 2

Based upon the results generated in phase 1, a new group of patients will comprise phase 2 of this study. Here, the oral-hygiene procedures described above will be performed in two groups of patients: (1) the most effective procedures in phase 1 group and (2) the mechanical cleaning with filtered water group. These procedures will be performed daily, over 5 days, when the outcomes will be evaluated. The clinical records will be checked and the pneumonia diagnoses will be determined by at least one of the following criteria: oximetry; body temperatures above 38 °C or below 35 °C; a leukocytosis or a leukopenia (leukocytes) count in the peripheral blood that is below 4000/mm^3^ or above 11,000/mm^3^; the existence of new, persistent or progressive lung infiltrates, or pleural effusion [51–54]. If any of the patients present an adverse reaction, they will be removed from the study and this will be reported in the published results paper. All of the personal information of the patients will be kept confidential. Figure 2 will describe the complete flow diagram for phase 2.

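### The VAP objective compares MB-mouthwash PDT with chlorhexidine, but phase 2 compares the phase 1 winner with filtered water and can never contain both

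*Protocol article*

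**What the plan says.** The last paragraph of the Background gives a VAP objective that names two procedures: the trial is to "show that oral hygiene using PDT with MB mouthwash may reduce VAP frequency to rates similar to, or higher than, chlorhexidine". The Background part of the Abstract repeats it. The same Background paragraph ties the objective to VAP diagnoses in the medical records after 5 days of daily care, which is the phase 2 outcome.

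Phase 2 is described differently. Under Interventions in phase 2 the two groups are "1) the most effective procedures in phase 1 group and (2) the mechanical cleaning with filtered water group". The Abstract (Methods) agrees: "the most effective procedure found in phase 1 and a mechanical cleaning with filtered water will be carried out daily". Study design and Data analysis plan give the same pair.

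Chlorhexidine is one of three phase 1 groups of 10 patients. Study design describes phase 1 as "using chlorhexidine as positive control for oral hygiene". The phase 1 outcomes, under Outcomes, are bacterial counts before and after treatment.

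The only VAP test in the Data analysis plan is a chi-square test for a difference between the two phase 2 groups. The phase 2 sample size rests on "percentages of patients with VAP before and after the implementation of oral-dental care", entered as 0.086 and 0.041. It gives 26 per group, raised to 35 per group for dropout.

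**The concern.** The objective needs VAP data on MB-mouthwash PDT and on chlorhexidine. I read 'rates similar to, or higher than' as a reduction at least as large as with chlorhexidine. The phase 2 arms are fixed by a rule that always makes filtered water the second group, so only one active procedure can enter. The test and the sample size also follow the water comparison: there is no margin for 'similar', and the assumed rates do not come from a comparison with chlorhexidine.

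The Discussion calls chlorhexidine the gold standard for oral hygiene in intensive care. A unit deciding whether to replace it would want exactly the comparison the objective promises. From this trial it would have phase 1 bacterial counts and no VAP comparison with chlorhexidine. A favourable result against water could still be read, under the stated objective, as support for similarity to chlorhexidine.

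**Working it through.** **1. Objective against arms.** Phase 2 allocates 35 patients to the phase 1 winner and 35 to filtered water (Sample size). These are patients allocated. The 35 includes a dropout allowance, so fewer may complete the 5 days.

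| Phase 1 winner | Mouthwash PDT | Aqueous MB PDT | Chlorhexidine | Water |
|---|---|---|---|---|
| Mouthwash PDT | 35 | 0 | 0 | 35 |
| Aqueous MB PDT | 0 | 35 | 0 | 35 |
| Chlorhexidine | 0 | 0 | 35 | 35 |

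Cases with both mouthwash PDT and chlorhexidine present: 0 of 3. If chlorhexidine was meant only as a benchmark that cannot be selected, the third row drops out and the count is 0 of 2. Some passages write 'procedures' in the plural, but this changes nothing: there are two groups and one is always water.

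**2. The plan's own phase 2 figure.** The 26 per group is for winner against water, so it does not bear on the chlorhexidine comparison. It also does not reproduce. For 0.086 against 0.041, two-sided 5% and 80% power (power is not stated for phase 2; 80% is assumed), with mean proportion 0.0635:

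n = [1.960·√(2·0.0635·0.9365) + 0.842·√(0.086·0.914 + 0.041·0.959)]² / 0.045² ≈ 460 per group.

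That is a separate problem and the present point does not depend on it.

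**3. Would a third arm of 35 be enough?** Half-width of the 95% interval for mouthwash minus chlorhexidine, both at true rate p: 1.96·√(2p(1−p)/35).

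- p = 0.041 (the with-care rate in Sample size calculation): 1.96·√(2·0.041·0.959/35) = 0.0929, about ±9.3 points. The assumed benefit of care is 8.6 − 4.1 = 4.5 points.
- p = 0.19 (the with-hygiene rate in the Discussion): 1.96·√(2·0.19·0.81/35) = 0.1838, about ±18.4 points. The benefit there is 25 − 19 = 6 points.

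With 26 per arm the half-widths are about 10.8 and 21.3 points. At 4.1% the normal approximation is rough, since 35 × 0.041 ≈ 1.4 events per arm are expected.

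**4. What 'similar' would need.** The protocol gives no margin. As an assumption, take one as wide as the whole benefit of care, which is generous. With one-sided 2.5%, 80% power and equal true rates, n per arm = (1.960 + 0.842)²·2p(1−p)/margin²:

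- p = 0.041, margin 0.045: 305 per arm.
- p = 0.19, margin 0.06: 672 per arm.

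Halving a margin multiplies the size by four.

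**The case against.** The strongest reply is that this is a wording fault and not a design fault. Every operational section describes phase 2 consistently. The outlier is one sentence, printed twice, softened by 'may' and introduced as an additional aim. The first aim in that paragraph, aqueous MB against the mouthwash, is tested in phase 1. This is largely right and is why the remedy is rewording. It does not remove the conflict: the sentence is stated as an objective and names its comparator.

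A second reply is that chlorhexidine may have been only a benchmark, since Interventions in phase 1 labels it "1) positive control group: chlorhexidine 0.12"% and not as a candidate. The text does not settle this. If it is so, a phase 2 with no PDT arm is ruled out, but both remaining cases still lack a chlorhexidine arm.

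A third is that phase 1 does compare the mouthwash with chlorhexidine. It does, on bacterial counts around a single treatment. VAP is not a phase 1 outcome.

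Three points on size stand. The 35 per group is the number recruited, so the intervals above are if anything too narrow. The sizes of 305 and 672 rest on assumed margins and describe a trial nobody proposes; they only show that a small extra arm is not a way out. And the risk of a misread significant result is limited: at the protocol's own rates the exact two-sided Fisher test has about 2% power with 35 per group.

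**Conclusion.** The concern holds. No phase 1 result leads to a VAP comparison of MB-mouthwash PDT with chlorhexidine, so one stated objective cannot be answered by the trial as designed. This follows from the text alone and needs no calculation. It assumes only that 'higher' means a larger reduction and that phase 2 has the two groups the article repeatedly describes. The figures are supporting: with 35 per arm the interval would be about twice the assumed benefit of care at a 4.1% rate and about three times at 19%. An adequate trial would need roughly 305 to 672 per arm under the assumed margins. The objective should be corrected before recruitment begins.

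**What to change.** Replace the VAP objective in the Abstract and the Background with wording that matches phase 2, for example: *To compare VAP frequency after 5 days of daily care between the oral-hygiene procedure selected in phase 1 and cleaning with filtered water. Chlorhexidine is compared with the two PDT procedures in phase 1 only, on viable bacterial count.* Remove the claim of VAP rates similar to or better than chlorhexidine.

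Add one sentence under Interventions in phase 2 saying whether chlorhexidine can be selected. The reworded objective holds either way. If phase 2 is meant to be a trial of PDT, selection should be limited to the two PDT procedures; that choice is the sponsor's.

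The cost is two sentences for the objective, one on eligibility, and the matching ethics and registry update. Trial status says recruitment has not started and already foresees a registry update. Arms, procedures, test and the 70 patients are unchanged. What is given up is a VAP claim against chlorhexidine that the planned arms could not support. Keeping that claim would need both procedures in phase 2, a justified margin and several hundred patients per arm. The rewording does not repair the phase 2 sample size for the water comparison, which needs its own review.
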